**Table 4. Comparisons of prevalence and intensity at Year 5 among arms.**

This table describes the primary outcomes.

|                       | Unadjusted prevalence model estimate (CI) | Adjusted prevalence model estimate (CI) | Unadjusted intensity ratio (CI) | Adjusted intensity ratio (CI) |
|-----------------------|--------------------------------------------------|------------------------------------------------|----------------------------------------|--------------------------------------|
| Arm 1 v. Arm 4 |                                                  |                                                |                                        |                                      |
| Arm 1 v. Arm 2 |                                                  |                                                |                                        |                                      |
| Arm 1 v. Arm 3 |                                                  |                                                |                                        |                                      |

|                |  |  |  |  |
|----------------|--|--|--|--|
| Arm 4 v. Arm 5 |  |  |  |  |
| Arm 4 v. Arm 6 |  |  |  |  |

*General approach to analysis:* The general approach is to use GEEs to estimate differences between the arms in year 5 only. We will report unadjusted estimates – with just village and arm fitted in the model – and adjusted estimates – where sex and age are also included in the model, along with weighting for number of children who provided data, because not all villages were able to sample 100 9-12 year old children.

ICC will be calculated using mixed models consistent with the GEE setup in the primary analysis.

All models will be based on individual level data on 9-12 year old children only.

*Sample code:* The following codes are provided as examples. Different studies may require further modification of the code below or may require different approaches.

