#### Unadjusted prevalence

The evaluation of unadjusted prevalence uses a binomial GEE with logit link function. Village\_ID is treated as the repeated subject, and we assume compound symmetry within a village. 'Lsmestimate' is used to test the pre-specified differences between arms.

```
ods trace off;
proc genmod data=allyears descending;
  where Study_Year = 5;
  class Study_Arm Village_ID / param=glm;
  model Sh = Study_Arm / dist=bin link=logit ;
  repeated subject=Village_ID / type=cs;
  lsmeans Study_Arm / cl;
  lsestimate Study_Arm "arm 2 vs. arm 1" -1 1 0 0 0 0 / cl;
  lsestimate Study_Arm "arm 3 vs. arm 1" -1 0 1 0 0 0 / cl;
  lsestimate Study_Arm "arm 4 vs. arm 1" -1 0 0 1 0 0 / cl;
  lsestimate Study_Arm "arm 5 vs. arm 1" -1 0 0 0 1 0 / cl;
  lsestimate Study_Arm "arm 6 vs. arm 1" -1 0 0 0 0 1 / cl;

  lsestimate Study_Arm "arm 3 vs. arm 2" 0 -1 1 0 0 0 / cl;
  lsestimate Study_Arm "arm 4 vs. arm 2" 0 -1 0 1 0 0 / cl;
  lsestimate Study_Arm "arm 5 vs. arm 2" 0 -1 0 0 1 0 / cl;
  lsestimate Study_Arm "arm 6 vs. arm 2" 0 -1 0 0 0 1 / cl;

  lsestimate Study_Arm "arm 4 vs. arm 3" 0 0 -1 1 0 0 / cl;
  lsestimate Study_Arm "arm 5 vs. arm 3" 0 0 -1 0 1 0 / cl;
  lsestimate Study_Arm "arm 6 vs. arm 3" 0 0 -1 0 0 1 / cl;

  lsestimate Study_Arm "arm 5 vs. arm 4" 0 0 0 -1 1 0 / cl;
  lsestimate Study_Arm "arm 6 vs. arm 4" 0 0 0 -1 0 1 / cl;

  lsestimate Study_Arm "arm 6 vs. arm 5" 0 0 0 0 -1 1 / cl;
estimate "O.R. arm 2 vs. arm 1" Study_Arm -1 1 0 0 0 0 / exp cl;
run;
```

Adjusted prevalence

The code is the same as for unadjusted prevalence, but with age, sex, and a weighting for village size added to the model.

villweight of individual = 1/# samples collected in village

```
ods trace off;
proc genmod data=allyears descending;
  where Study_Year = 5;
  class Study_Arm Village_ID Sex Age / param=glm;
  model Sh = Study_Arm Sex Age / dist=bin link=logit ;
  repeated subject=Village_ID / type=cs;
  weight villweight ;
  lsmeans Study_Arm / cl;
run;
```

ICC of prevalence

```
/*macro*/
%macro icc_bin(data, cluster, outcome, out, m, stval=%str(), pred=%str());
proc nlmixed data=&data.;
  parms b0=0 &stval. var1=1;
  eta = exp(b0 + &pred. r);
  pred = eta / (1+eta);
  model &outcome. ~ binary(pred);
  random r ~ normal(0,var1) subject=&cluster.;
  estimate 'ICC' var1/(var1 + (constant('PI')**2)/3);
  estimate 'Deff' 1 + (&m.-1) * (var1/(var1 + (constant('PI')**2)/3));
  ods output AdditionalEstimates=&out.;
run;

data &out.;
  set &out.;

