  cluster="&cluster.";
  outcome="&outcome.";
  m=&m.;
run;
%mend;
```

```
%icc_bin(sac, HHID, asc, hhl, 2.91, stval=%str(), pred=%str());
```

Unadjusted intensity

The code is the same as for unadjusted prevalence, but the distribution and link are changed.

```
ods trace off;
proc genmod data=allyears descending;
  where Study_Year = 5;
  class Study_Arm Village_ID / param=glm;
  model Sh = Study_Arm / dist=nb link=log ;
  repeated subject=Village_ID / type=cs;
  lsmeans Study_Arm / cl;
run;
```

Adjusted intensity

The code is the same as for the adjusted prevalence, but the distribution and link are changed.

```
ods trace off;
proc genmod data=allyears descending;
  where Study_Year = 5;
  class Study_Arm Village_ID Sex Age / param=glm;
  model Sh = Study_Arm Sex Age / dist=nb link=log ;
  repeated subject=Village_ID / type=cs;
  weight villweight ;
  lsmeans Study_Arm / cl;
run;
```

Figure 4. Village-level mean intensity by year, by arm.

Provide a line graph showing arithmetic mean intensity, by Year, by Arm.

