### Figure 3. Intensity categories, by Arm, by Year.

This is a stacked bar chart, showing low, medium, and high intensity infections, by Arm, for Years 1-5, and each study separately. Intensity categories are defined as:

- Sh: Low 1-50 eggs/10 ml, high  $\geq 51$  eggs/10 ml

A supplemental table including the numbers used to make the chart should be available should modelers or other analysts want to use the exact data.

Table 4. Comparisons of prevalence and intensity at Year 5 among arms.

This table describes the primary outcomes.

|                         | Unadjusted prevalence model estimate (CI) | Adjusted prevalence model estimate (CI) | Unadjusted intensity ratio (CI) | Adjusted intensity ratio (CI) |
|-------------------------|-------------------------------------------|-----------------------------------------|---------------------------------|-------------------------------|
| Study A: Arm 1 v. Arm 2 |                                           |                                         |                                 |                               |
| Study B: Arm 1 v. Arm 2 |                                           |                                         |                                 |                               |
| Study C: Arm 1 v. Arm 2 |                                           |                                         |                                 |                               |

*General approach to analysis:* The general approach is to use mixed models to estimate differences between the arms in year 5 only, analyzing each study separately. We will report unadjusted estimates – with just village, study group and arm fitted in the model – and adjusted estimates – where sex and age are also included in the model. The mixed model will implicitly weight for any villages that were not able to sample 100 9-12 year old children.

ICC will be calculated using mixed models in the primary analysis.

All models will be based on individual level data on 9-12 year old children only.

*Sample code:* The following codes are provided as examples.

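### The sample ICC code in both SAPs is not set up for the village trial, and its design-effect line uses an ICC on the wrong scale

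*Combined protocol and SAP*

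**What the plan says.** In the main SAP, section VI.b (Table 4, general approach), the rule is that "ICC will be calculated using mixed models consistent with the GEE setup in the primary analysis". The setup referred to is the unadjusted prevalence GEE printed just after it: Year 5 records, Village_ID as the repeated subject, "model Sh = Study_Arm / dist=bin link=logit", and the statement that "we assume compound symmetry within a village". Section II.c gives a target of 100 children aged 9-12 per village.

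The ICC macro follows. The cluster is a user-supplied parameter, "random r ~ normal(0,var1) subject=&cluster". The ICC is computed as var1/(var1 + π²/3), and the next line puts the same expression into 1 + (m − 1) × ICC and labels it Deff. The macro is then called as "icc_bin(sac, HHID, asc, hhl, 2.91, stval=%str(), pred=%str".

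The Niger SAP, section VI.b, prints the same macro and the same call. Its prose rule is shorter, "ICC will be calculated using mixed models in the primary analysis", and its primary analysis is a mixed model with a village effect and a study-group term.

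Both SAPs introduce their code as examples. The main SAP adds that studies may need to modify it or use other approaches.

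**The concern.** The ICC is a promised output, and this macro and call are its only worked specification. There are two separate faults.

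First, the call does not describe this trial. Its cluster, outcome and cluster size all differ from those of the primary model. The empty predictor slot leaves arm out, so any difference between arms would be counted as variation between clusters. The macro has no Year 5 filter, and nothing says that the dataset named in the call is restricted to Year 5.

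Second, the Deff line is wrong for a prevalence whatever arguments are supplied. The variance of a proportion from a cluster sample is inflated by 1 + (m − 1) × ICC when the ICC is the correlation of the 0/1 outcome. The logistic-scale ICC is larger, and the gap widens as prevalence falls.

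At stake is whether the ICC, and any design effect quoted with it, describes clustering of infection within villages. The prefaces of both SAPs ask investigators to use the SAP's definitions and approaches, so an uncorrected template could be carried into several country analyses.

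**Working it through.** The documents state no ICC, design effect or between-village variance, so there is no figure of the plan's to reproduce.

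**Inputs**
- m = 2.91, HHID, asc and an empty predictor slot: the printed call, both SAPs.
- Village_ID, Sh, Study_Arm, Year 5: main SAP, unadjusted prevalence code.
- 100 children per village: main SAP, section II.c (nominal target).
- var1: not given. The value 1 in the macro is only a starting value. Assumed range 0.5 to 2.
- Prevalence: 5% to 30%, assumed.

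**Step 1: the call beside the primary model (main SAP)**

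| Item | Printed call | Primary prevalence model |
|---|---|---|
| Cluster | HHID | Village_ID |
| Outcome | asc | Sh |
| Cluster size | 2.91 | about 100 |
| Arm | absent | Study_Arm |
| Year | no filter in macro | Year 5 only |

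**Step 2: the macro's formulas at var1 = 1**

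Latent ICC = 1/(1 + π²/3) = 1/4.290 = 0.233, whatever the prevalence.

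Deff at m = 2.91: 1 + 1.91 × 0.233 = 1.45.

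Deff at m = 100: 1 + 99 × 0.233 = 24.1.

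**Step 3: the observed-scale ICC**

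Let p_j = 1/(1 + exp(−(b0 + r_j))), with r_j normal, mean 0, variance var1. Solve for the b0 that gives mean prevalence p. Then ICC = Var(p_j)/[p(1 − p)], evaluated by Gauss-Hermite quadrature, and Deff = 1 + 99 × ICC.

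| var1 | Prevalence | Latent ICC | Macro Deff, m = 100 | Observed ICC | Observed-scale Deff | Ratio |
|---|---|---|---|---|---|---|
| 0.5 | 5% | 0.132 | 14.1 | 0.027 | 3.7 | 3.8 |
| 0.5 | 30% | 0.132 | 14.1 | 0.090 | 9.9 | 1.4 |
| 1 | 5% | 0.233 | 24.1 | 0.058 | 6.7 | 3.6 |
| 1 | 10% | 0.233 | 24.1 | 0.092 | 10.1 | 2.4 |
| 1 | 20% | 0.233 | 24.1 | 0.134 | 14.3 | 1.7 |
| 1 | 30% | 0.233 | 24.1 | 0.157 | 16.6 | 1.45 |
| 2 | 5% | 0.378 | 38.4 | 0.121 | 12.9 | 3.0 |
| 2 | 30% | 0.378 | 38.4 | 0.255 | 26.2 | 1.5 |

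**Step 4: which ICC matches the actual inflation**

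A simulation of 150 villages of 100 children (var1 = 1, mean prevalence 22%, 200 runs) gave an actual variance inflation of 14.9. The formula gives 14.8 with the observed-scale ICC (0.140) and 24.1 with the latent ICC (0.233).

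**Step 5: a prevalence range from the documents**

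Supplemental Table S6 gives Year 5 prevalences of 10.5% to 23.2% for the once- and twice-yearly arms of Niger Groups B and C. With m = 100 and var1 from 0.5 to 2, the macro's Deff would be 1.6 to 2.4 times the observed-scale value over that range.

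The two faults act in opposite directions. At var1 = 1, setting m to 100 and leaving the macro body alone moves Deff from 1.45 to 24.1, past the observed-scale values of 6.7 to 16.6.

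**The case against.** The strongest reply is that this is sample code. Dataset, cluster, outcome, cluster size and predictors are all macro parameters, and the prose rule in the main SAP already points the analyst to the village model. HHID and asc are not defined in the text available, so an analyst would have to replace them to get a village result. That largely answers the first fault as a threat to results. It does not make the example right, and it does not reach the second fault, because the scale error is in the macro body and survives any choice of arguments.

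It is also fair that a logistic mixed model naturally yields a latent-scale ICC and that this is a legitimate quantity. Consistency with the GEE setup can be read as the same clusters, data and fixed effects, without requiring the same scale. That stands: a labelled latent-scale ICC is not an error, least of all in Niger, where the primary model is itself mixed. Putting it into the design-effect formula for a prevalence remains wrong. Leaving arm out also remains inconsistent with the main SAP's rule on either reading.

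Finally, the prose asks only for an ICC. Deff appears only as macro output, and Table 4 has no column for either. This limits the importance of the point.

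**Conclusion.** The concern holds as a low-severity defect in the sample code. As printed, the call would not give the village trial's ICC. With the arguments put right, the macro's Deff would still be too large: about 3.0 to 3.8 times at 5% prevalence and 1.4 to 1.5 times at 30%. These figures assume 100 children per village, a normal village effect on the logit scale and var1 between 0.5 and 2. The ratios are illustrative because the documents give no variance estimate.

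The documents do not support three stronger readings that a reader might infer.
- That wrong ICCs or design effects were reported. No such value appears in either SAP or in Supplemental Tables S1 to S6.
- That the arm comparisons are affected. They handle clustering directly, through the GEE with village as repeated subject or the Niger village random effect, and do not use Deff.
- That a household analysis was planned or run, or that later trials will be sized from these figures. Household is a guess from a variable name, and the documents describe no such use of the ICC or Deff.

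**What to change.** In both SAPs, call the macro on Year 5 children aged 9-12 with Village_ID as cluster, Sh as outcome, the actual mean number tested per village as m, and arm terms in the predictor slot (plus Study_Group in Niger). The macro writes the random effect straight after that slot, so the terms must end with a plus sign, and their coefficients need starting values.

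For any Deff, use an observed-scale ICC. In the main SAP this can be the exchangeable correlation from the primary GEE, which that model already estimates, or a conversion that integrates over the fitted village effect. In Niger, where the primary model is mixed, only the integrated conversion applies.

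If the latent-scale ICC is also reported, label it as such and take it out of the Deff line.

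The cost is a few lines of code and one sentence of text in each SAP. No new data are needed and no arm comparison changes.

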## V. DEFINITIONS OF PREVALENCE, INTENSITY, AND COVERAGE

The following definitions will be used for individual-level data:

- Individual mean eggs per gram (epg) (Sm studies):  $24 \times \text{total number of eggs found in all slides} / \text{number of slides examined}$ . Individual mean epg will be used for reporting, as it is the standardly used metric for infection intensity.
- Individual egg count (Sm studies):  $\text{Total number of eggs found in all slides examined} / \text{number of slides examined}$ . Individual egg count will be used for analysis, as epg does not have a continuous distribution. Note that some software packages may require individual egg count to be rounded prior to analysis. If the analysis requires integers, then the egg count used for formal statistical analysis should be  $6 \times \text{Total number of eggs found in all slides examined} / \text{number of slides examined}$ , rounded to the nearest whole number. If estimated counts are over 1,000 after adjustment for number of slides, they should be truncated at 1,000, as is common practice in schistosomiasis clinical research studies.
- Individual mean eggs per 10 ml (Sh studies):  $\text{Number of eggs found} \times 10 / \text{volume of urine filtered}$ . If estimated counts are over 1,000 after volume adjustment, they should be truncated at 1,000. Mean eggs per 10 ml will be used for both analysis and reporting, as this measure is both continuous and a standard metric. Note that some software packages may require mean eggs per 10 ml to be rounded prior to analysis, but this will only affect individuals with less than 10ml of urine filtered.
- Egg positive: a child will be deemed to be egg-positive if one or more eggs were found in any of the slides examined.

The following definitions will be used for reporting on cross-sectional and cohort studies:

- **Prevalence of *Schistosoma* infection:** Percentage of egg-positive children among the 9-12 year olds tested in each community each year.
- **Mean intensity of *Schistosoma* infection:** *Arithmetic* mean of individual mean epg or eggs per 10 ml among the 9-12 year-old children. Two values are to be reported:
  - i) Village-level intensity: This is the mean egg count for all tested 9-12 year-old subjects (including those with zero egg counts), which is a measure of community-level contamination potential.

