### a. Key research questions for Gaining and Sustaining studies

The primary research questions are:

- 1a. Does the final (Year 5) prevalence of schistosomiasis among children age 9-12 differ by Study Arm?
- 1b. Does the final (Year 5) mean intensity of Sm or Sh infection among all children aged 9-12 differ by study arm?

More specifically, the planned analysis will involve a series of arm-to-arm comparisons, prioritized according to what questions are likely to be most important for decision-makers. Because there is risk of “false discovery” of statistically significant association when multiple comparisons are made (Type I error), the number of comparisons formally tested will be restricted. In both studies, the focus of analysis will be on comparison of the current standard of care with alternative treatment strategies in decreasing order of priority. P value cutoffs will not be adjusted. However, this potential limitation of the analyses will be included in the discussion of results, and interpretation will be guided by the strength of the arm-specific effects.

In Sm1 and Sh1 areas, the standard for morbidity control in relatively low-prevalence areas is annual SBT (Arm 1). Instituting “holidays” is hypothesized to lessen the impact of a treatment program on prevalence and intensity. This yields the following comparisons in priority order:

1. Because alternate years of SBT and Holidays would be the easiest to institute, the first comparison in Sm1 should be between **Arm 1 and Arm 3**.
2. Subsequently, we will compare **Arm 1 and Arm 2**.

For high prevalence communities, the standard for schistosomiasis control is annual SBT, as conducted in Arm 4 of the Gaining and Sustaining studies. Instituting CWT may increase the impact of treatment on local prevalence and intensity of *Schistosoma* infections. Under this consideration, the following comparisons are to be considered for the Sm2 and Sh2 trials:

1. Because annual SBT is the standard, the first comparison should be between **Arm 1 and Arm 4**.
2. Subsequently, we will compare **Arm 1 and Arm 2, Arm 1 and Arm 3, Arm 4 and Arm 5, and Arm 4 and Arm 6**.

The original statistical analysis plan for evaluating the Gaining and Sustaining studies is found in Appendix H.

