### Unadjusted intensity

The code is the same as for unadjusted prevalence, but the distribution and link are changed. Study\_Arm and Study\_Group should be tested for – if found to be significant, comparisons between arms should be reported separately for each study.

```
proc mixed data=allyears descending;
  where Study_Year = 5;
  class Study_Arm Village_ID Study_Group / param=glm;
  model Sh = Study_Arm Study_Group / dist=nb link=log;
  random=Village_ID / type=cs;
  lsmeans Study_Arm / cl;
run;
```

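### The sample code for the primary intensity analysis keeps the prevalence model's response variable, not the egg measure that Section V names

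*Combined protocol and SAP*

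**What the plan says.** Primary question 1b in Section VI.a of the Gaining and Sustaining SAP asks: "Does the final (Year 5) mean intensity of Sm or Sh infection among all children aged 9-12 differ by study arm". Section VI.b says of Table 4, which has separate prevalence and intensity columns: "This table describes the primary outcomes".

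Section V fixes the variable for intensity. For *S. mansoni*: "Individual egg count will be used for analysis, as epg does not have a continuous distribution". For *S. haematobium* it is mean eggs per 10 ml.

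The Table 4 sample code for unadjusted prevalence has "model Sh = Study_Arm / dist=bin link=logit". The unadjusted intensity block is introduced with "The code is the same as for unadjusted prevalence, but the distribution and link are changed" and has "model Sh = Study_Arm / dist=nb link=log". The adjusted intensity block keeps `Sh` and adds sex and age. The Niger SAP does the same, for example "model Sh = Study_Arm Study_Group / dist=nb link=log".

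The code carries a caveat: "Different studies may require further modification of the code below or may require different approaches".

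**The concern.** The sentence lists what changes between the two models and leaves out the outcome, and the code agrees with the sentence. One variable cannot serve both analyses. If `Sh` is infected yes/no, the intensity model has the wrong response. If `Sh` is an egg count, the binomial prevalence model does.

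An analyst who followed the intensity block literally would compare the share of children infected a second time, on a ratio scale, and label the result intensity. A strategy that lowered egg output without lowering the share infected would show no effect. A strategy that moved the two in opposite directions would be reported with the wrong sign for intensity. The SAP was written so that country teams would analyse their data comparably, so its worked example should show the intended response.

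**Working it through.** **1. Response variable, model by model.** The plan states no figure on this point, so there is none to reproduce. The left-hand sides compare as follows.

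| SAP and block | Procedure | Response | Distribution, link |
|---|---|---|---|
| Gaining and Sustaining, prevalence (unadjusted, adjusted) | GENMOD | `Sh` | binomial, logit |
| Gaining and Sustaining, intensity (unadjusted, adjusted) | GENMOD | `Sh` | negative binomial, log |
| Niger, prevalence (unadjusted, adjusted) | MIXED | `Sh` | binomial, logit |
| Niger, intensity (unadjusted, adjusted) | MIXED | `Sh` | negative binomial, log |

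No egg variable appears in any of them. In the text available, `Sh` is defined only as the species abbreviation. The data dictionary is listed as an appendix but is not reproduced.

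**2. What the intensity model estimates with a 0/1 response.** With a log link and arm as the only covariate, log E(Y) = b0 + b1 × arm. If Y is 0/1, E(Y) is the proportion infected, so exp(b1) = p(arm 1) / p(arm 0). With equal village sizes an exchangeable GEE returns this ratio exactly, whatever the dispersion.

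A simulation agrees. It used 25 villages per arm, 30 trials per setting, an assumed ICC of 0.1, and prevalences and means like those of Table S6 Groups B and C.

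| Setting, 100 children per village | Negative binomial/log on 0/1 | Raw prevalence ratio | Negative binomial/log on eggs |
|---|---|---|---|
| Group B-like | 0.58 | 0.58 | 0.365 |
| Group C-like | 0.80 | 0.80 | 1.49 |

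These are medians. The first two columns agreed to four decimals in every trial. With 40 to 100 children per village, the 0/1 model stayed within 0.10 of the raw prevalence ratio.

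**3. How far the two quantities differ in the reported data.** Tables S1 to S5 give 15 + 5 + 5 + 3 + 3 = 31 contrasts. Section VI.a prioritises five for each Sm2 or Sh2 study and two for each Sm1 study: 3 × 5 + 2 × 2 = 19. Of the 19, three are significant in one column only.

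| Contrast | Prevalence ratio (CI) | Intensity ratio (CI) |
|---|---|---|
| S1 SHSH v SSSS | 1.68 (1.01, 2.80) | 2.08 (0.77, 5.63) |
| S3 CCHH v CCCC | 1.45 (0.85, 2.47) | 2.15 (1.10, 4.18) |
| S3 SSHH v SSSS | 1.73 (1.08, 2.77) | 1.32 (0.66, 2.61) |

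Four more lie outside the prioritised list: S1 CCHH, SSHH and SHSH, each against CCSS (prevalence only), and S4 SHSH v SSHH (intensity only). That makes 3 + 4 = 7 of 31.

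**4. Direction, from Table S6 Group C at Year 5, twice-yearly over once-yearly.**
- Prevalence: (392/3,724) / (425/3,689) = 10.53% / 11.52% = 0.91.
- Community-level mean intensity: 2.18 / 1.37 = 1.59.

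These ratios are crude, without adjustment for clustering or baseline. They show only that the two measures need not move together.

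**The case against.** The strongest reply is that the governing text is right. Section V names the egg measure, gives an integer form for software that needs one, and sets a truncation at 1,000. Those rules make sense only if eggs are the response. Question 1b and the Table 4 column titles also say intensity. The code is offered as examples open to modification. Four of the five studies covered are of *S. mansoni*, so a variable called `Sh` has to be adapted anyway. The ICC call, with a household identifier and a cluster size of 2.91, is plainly carried over from elsewhere. All of this stands. It makes the point an error of code and description. It does not excuse the introductory sentence, which is prose and says the wrong thing.

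A reader might infer that the published intensity results are really prevalence results. The documents contradict that. In Table S1, CCSS v CCCC has a prevalence ratio of 0.59 and an intensity ratio of 0.36. In Table S3, SHSH v SSSS has 1.12 and 0.70. Tables S1, S4 and S5 label the intensity column an arithmetic mean ratio. The printed code was evidently not run unchanged.

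A reader might also infer that every printed block would output a second prevalence ratio. That is too strong in three ways. The prevalence model has a logit link and gives an odds ratio. The printed intensity blocks stop at log-scale least-squares means, so a ratio needs differencing and exponentiating. The Niger blocks put distribution and link options in PROC MIXED, which fits normal models only, so they would not yield a ratio at all.

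**Conclusion.** The point holds as a mismatch between the sample code, with its introductory sentence, and the Section V definition. Taken literally, the two Gaining and Sustaining intensity blocks would compare proportions infected on the log scale. The two Niger intensity blocks name the same wrong response but would fail before giving a result. The endpoint is correctly defined, and nothing in the documents shows an error in the reported intensity ratios.

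The size is what would be at stake if the code were followed: a different significance status for 3 of 19 prioritised contrasts (7 of 31 reported), and a possible reversal of direction as in Table S6 Group C. This rests on two assumptions. `Sh` is the 0/1 infection indicator, as the binomial model requires. The reported prevalence ratios are a fair stand-in for what the literal code would return.

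**What to change.** In all four negative binomial blocks (unadjusted and adjusted, in both SAPs), replace `Sh` with the Section V intensity variable: individual egg count for *S. mansoni*, in the integer form where the software needs it, and eggs per 10 ml for *S. haematobium*. Give the 0/1 egg-positive indicator its own name in the prevalence blocks. Reword the introductory sentences to say that the outcome variable changes along with the distribution and the link. State which variable the reported intensity analyses used.

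Separately, in the Niger SAP replace PROC MIXED in both the prevalence and the intensity blocks with a procedure that fits binomial and negative binomial mixed models, such as PROC GLIMMIX.

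The cost is a few words, one variable name in each intensity block and a change of procedure for Niger. No new data are needed.
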